#### Ethical considerations

Ethical clearance has been obtained at each of the participating hospitals: St Vincent’s Hospital Melbourne, Austin Health, Melbourne Health - Australia. The trial has also been registered with the Australian New Zealand Clinical Trials Group ACTRN12615000200583.

#### Analyses plan

The main analyses will be performed on pooled data across sites for the intervention and control groups, following an analysis of the baseline data to identify any differences between sites. We will undertake analyses as follows. Summary statistics will be calculated to compare the characteristics of carers in each group. Linear mixed models will be used to (1) compare patterns of change over time by testing the intervention group by time interaction and (2) estimating and testing differences in scores between groups at T2 and at T3 via linear contrasts, and accounting for the non-independent nature of the data in clusters. Mixed models yield unbiased estimates for data which are missing [48], and is relevant for cluster trials [49]. Sub analyses will be undertaken dependant upon obtaining a suitable sample size. In the event of ‘no intervention effect’, where possible, a sub-analysis will be conducted to compare outcomes in the control group carers who did not have a meeting (i.e. a ‘per protocol’ analysis) with those in the intervention group carers who had a meeting. In the event of ‘no intervention effect’ , a sub-analysis will be conducted on those that were moderately or highly distressed at time 1 to compare outcomes in the control group and intervention group for distressed carers. A sub analysis will also be undertaken to explore any differences in outcomes between participants recruited from the specialist palliative care in-patient facility and those recruited from a palliative care hospital consultancy service.

### Aim 2

To determine the cost-benefit and resource implications of implementing SFM meetings into routine practice.

Health economic modeling will be applied to estimate the cost-benefit of SFM. Decision analysis [50] will be used to compare the downstream consequences of SFM versus standard of care, by extrapolation of efficacy data from the trial. The incorporation of Markov [51] and life-tabling [52] techniques will allow for the modeling of outcomes beyond the duration of the trial. The key output in cost-benefit analyses is net costs, comprising the costs of SFM minus costs saved from the reduction in downstream health services utilisation. Only direct healthcare costs will be measured, and from the perspective of the Australian healthcare system. These will predominantly be costs of inpatient and outpatient hospital care, medications and community-based healthcare services. All health economic analyses will be undertaken in accordance with recommended approaches, such as 5 % discounting of estimated future costs and health gains. To account for any uncertainty in the data, inputs for health economic modeling, sensitivity and uncertainty analyses will be undertaken via Monte Carlo simulation [53].

We will also conduct a process evaluation to determine the resource requirements of administering the SFM. Such data will include the mean time to conduct the intervention, the number and the types of health disciplines involved in the family meeting and whether or not the patient also participated. We will also explore the administrative time involved in setting up and facilitating the SFM.

At the completion of the intervention phase two focus groups will be conducted with health professionals and interviews (approx. 20) with family carers from the intervention sites will be undertaken to explore the perceived impacts and benefits of the SFMs. They will also be used to discern external and internal policy changes; clinician (staff resource, beliefs and attitudes), patient and carer factors (access, timeliness, understanding, information). This will assist with monitoring temporal issues relevant to the study.

All health professionals at each of the two intervention sites who have attended at least two of the SFMs will be invited to participate in a focus group (via a personalised email). The Plain Language Statement and consent form will be attached to the email. At the beginning of the focus group, the project officer will go through the Plain Language Statement; which will provide all potential participants with the assurance that their involvement is entirely voluntary and their participation or otherwise will in no way hinder their employment. Health professionals will be asked to complete the consent form. Once informed consent is obtained from the palliative care health professionals, the project officer will conduct a focus group. The focus group will be taped and transcribed and any identifying information deleted from the transcripts. The focus group will take about 30–60 min.

One in six family carers who complete the intervention will be invited to participate in an interview after the completion of their time 2 questionnaires via a question on the questionnaire with a Yes/No response format and an open-ended space which requests a phone number and best time to call. The research assistant will then call the family carer at the suggested time and ask the carer whether they are still interested in participating in an interview and if they are, they will organise a convenient time. Interviews may be conducted at the hospital or over the telephone. Interviews will be recorded and transcribed. A semi structured interview guide has been developed by the project team and incorporates questions related to: perceptions of the way the family meeting was convened and conducted; reflections on any positive or negative outcomes and recommendations for improving family meetings. It is expected that the interview take approximately 30 min.

Focus groups will be recorded and transcribed and analysed for impacts, benefits and additional content. Interviews will be recorded digitally verbatim and transcribed. NVivo software will be used to assist with storage and coding. The interviews will be analysed using the five steps of thematic analysis recommended by Boyatzi [54] (1) reducing the raw information, (2) creating a code, (3) determining the reliability of the code, (4) identifying themes within subthemes and (5) comparing themes across subsamples. The first two interviews (20 %) from each site will be coded by two members of the research team. A Kappa value of 0.6–0.8 indicating substantial agreement between raters [55] will be achieved at step 3 prior to the research assistants completing steps 4 and 5 for the remainder of the interviews.

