#### Sample size, power calculation and feasibility

The primary outcome for H1 is measured via the GHQ, a 12-item scale with a possible range of 0-36. Our previous study [46] of 275 family carers in which the mean GHQ difference was 2.8 (SD = 5.6), represents a medium effect size (ES) of 0.5 which is a common estimate of a minimal important difference [47]. The sample size calculations are based on a smaller mean difference between groups of 2.4, as some carers in the control group will have family meetings as part of standard care. Estimated sample size for two-sample comparison of means Test Ho: m1 = m2, where m1 is the mean in population 1and m2 is the mean in population 2 is 97 per group (total *n* = 194). This calculation assumes that alpha = .05 (two sided), power = .90 (90 %), m1 = 16.8, m2-14, sd1 = 6, sd2 = 6, n2/n1 = 1.00. This sample size allows for sub-group analyses of the consult service compared to the inpatient service or other similar sub-group analysis.

For the three recruitment sites, we have approximately 1900 palliative care inpatient admissions per year and 3000 palliative care consult service admissions per year. However, many consult service admissions become inpatient admissions. Approximately a third of the total admissions per year would be both consult admissions and inpatient admissions, leaving 3280 admissions per year that reflect separate individuals. Based on eligibility rates and response rates of similar previous studies we can assume 50 % of these are eligible (*n* = 1640), ineligibility mostly due to being imminently dying. A further 33 % of those who are eligible consent to participate (*n* = 546). Of the 546 that consent, we assume that 60 % will complete data collection at Time 1 (*n* = 327). Assuming 30 % attrition at T2 (leaving *n* = 228) and 50 % attrition at T3 (since it is during bereavement, attrition may be quite high), 114 cases can be completed per year, providing the required sample size of 228 from the recruitment pool in 2 years.

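### GHQ, the one primary outcome, is tested three ways with no primary test, time point or order, and the T2 and T3 contrasts state no adjustment for T1 GHQ

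*Protocol article*

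**What the plan says.** In the sample size section: "The primary outcome for H1 is measured via the GHQ". Under Family carer measures, the GHQ is scheduled at T1, T2 and T3, and T3 falls after the patient's death.

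The Analyses plan uses linear mixed models for two purposes. The first is to "compare patterns of change over time by testing the intervention group by time interaction". The second is "estimating and testing differences in scores between groups at T2 and at T3 via linear contrasts". No sentence ranks these tests, names a primary time point or divides alpha. The statement of Aim 1 covers both short- and longer-term effects and does not put T2 ahead of T3.

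The sample size section describes one test: "Estimated sample size for two-sample comparison of means Test Ho: m1 = m2". The only alpha in the article is there: "This calculation assumes that alpha = .05 (two sided". It gives no time point and no baseline adjustment.

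The Analyses plan also makes two further analyses conditional on the intervention showing no effect. One compares control carers who had no meeting with intervention carers who had one. The other is restricted to carers distressed at T1. Neither condition is tied to a test.

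On baseline differences, the Research design section says that differences between sites can be controlled for if this proves necessary. T1 GHQ is not named.

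**The concern.** The plan and the sample size describe different decision rules: three tests of the primary outcome against one 5% comparison. A reader cannot tell which result would settle H1. The three can disagree, and T2 and T3 answer different questions. T3 is measured in bereavement, in a smaller group of completers (30% attrition assumed at T2, then 50% at T3). If the interaction were null and T3 significant, it would be unclear both whether H1 was supported and whether the conditional analyses should be run.

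A second, separate matter is precision and baseline balance. T1 GHQ is collected, but the contrasts are worded as differences in scores at T2 and T3. Only three sites are randomised, and two of them are compared before and after, so T1 balance between the pooled groups cannot be relied on.

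**Working it through.** **Inputs from the article.** Alpha .05 two-sided; power .90; means 16.8 and 14; SD 6 in both groups, 1:1 ("sd1 = 6, sd2 = 6, n2/n1 = 1.00"); n "is 97 per group"; three GHQ occasions. **Assumed, because not given:** the GHQ correlation r between occasions, equal for all pairs, .3 to .8. Clustering by site is ignored throughout.

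**1. The plan's own figure.** n per group = 2 × [SD × (1.960 + 1.282) / d]².
- d = 16.8 − 14 = 2.8: 2 × (6 × 3.242 / 2.8)² ≈ 96.5, so 97. This reproduces the stated n for one 5% test.
- The text says otherwise: "The sample size calculations are based on a smaller mean difference between groups of 2.4". With d = 2.4 the formula gives 132, and 97 per group has 79.6% power. That mismatch is a separate point. It matters here only because it leaves little precision to spare.

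**2. False-positive rate of the three tests.** Standardised group differences at T1, T2 and T3 were drawn under no effect (400,000 draws per r). The interaction was a 2-df Wald test of the two changes from T1; the contrasts were z-tests at T2 and T3; each was at 5%.

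| r | T2 or T3 significant | Any of the three | A contrast significant, if tested only after a significant interaction |
|---|---|---|---|
| .3 | 9.5% | 12.3% | 2.2% |
| .5 | 9.1% | 12.4% | 1.7% |
| .7 | 8.2% | 12.1% | 1.1% |
| .8 | 7.8% | 11.9% | 0.9% |

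Three independent tests would give 1 − .95³ = 14.3%, which overstates the rate because these tests are correlated. The interaction alone rejects in 5.0% of null trials. At r = .5, therefore, 12.4% − 5.0% = 7.4% of null trials have a significant contrast with a non-significant interaction.

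**3. Does the contrast use T1?** Mixed models with free group-by-time means were fitted to simulated complete data (97 per group, r = .5). The T2 contrast equalled the raw T2 mean difference (largest gap about 10⁻¹⁴). Under those conditions T1 adds nothing to the contrast.

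**4. What T1 adjustment is worth.** The variance is multiplied by 1 − r².
- Unadjusted SE = 6 × √(2/97) = 0.862. At r = .5 the adjusted SE = 0.862 × √.75 = 0.746, a 25% cut in variance.
- At r = .3 the cut is 9%; at r = .7 it is 49%.
- Power at 97 per group for d = 2.4 rises from 79.6% to 83%, 90% and 97% at r = .3, .5 and .7.

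**5. Imbalance.** A chance T1 difference of g points shifts the unadjusted T2 contrast by about r × g. For example, g = 1 and r = .5 give 0.5 points, which is 0.5 / 2.4 = 21% of the stated target difference.

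**The case against.** The strongest reply is that the article states neither a threshold for these tests nor that any one of them would count as success. A reader might infer that each is tested at 5% and any one wins, but .05 appears only in the sample size section. The interaction is listed first. If the contrasts were examined only after a significant interaction, overall error would stay at 5%. This stands as a limit on the 12% figure, which is conditional on an assumed rule. It does not supply the missing rule, because the article states no such gate either.

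A reader might also infer that the contrasts ignore T1 GHQ. The article does not say so. T1 is one of the occasions in the change-over-time model, the interaction uses it, and when T2 or T3 values are missing, as the article expects, T1 informs the contrasts. The reduction to a raw difference needs free T1 means and complete data. The exact parameterisation may properly sit in a fuller analysis plan. What stands is that the contrasts are worded on scores with no baseline adjustment, and the only stated safeguard is site control if judged necessary.

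Nor does the lack of T1 adjustment inflate the false-positive rate when groups are balanced in expectation. The inflation in step 2 comes from the number of tests.

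Finally, choosing T2 over T3 is a judgement, since the aim covers both. That is fair: the defect is that no choice is made.

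**Conclusion.** The point holds in this form. The article commits to three tests of one primary outcome, sizes one unnamed comparison, and makes further analyses depend on a null result that no test defines. This is a conflict within the printed plan, more than detail left for later.

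If any one test at 5% sufficed, the false-positive rate would be about 12%, roughly 2.4 times nominal, or about 8 to 9.5% for the two contrasts alone. These figures rest on that assumed rule, on equal correlations of .3 to .8 and on ignoring site clustering. The documents do not support saying that the trial will run at 12%.

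The missing T1 adjustment is a separate, smaller matter. It costs a variance share of r² under free T1 means and complete data, and it lets T1 imbalance into the contrast. The size depends on a correlation that the article does not give.

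**What to change.** Change the Analyses plan to say the following:
- One contrast is primary, for example GHQ at T2, estimated with adjustment for T1 GHQ and tested at two-sided .05.
- The other time point is secondary, has the same adjustment, and is tested only if the primary contrast is significant.
- The group-by-time interaction is reported descriptively.
- The condition for the two follow-up analyses is a non-significant primary contrast.

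The sample size section should name the same contrast and time point.

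**Cost.** A few sentences and no new data. The real downside is that an effect seen only at the other time point becomes secondary, and the gate could block a formal claim about it. If the investigators want all three tests to stay primary, Bonferroni at .05/3 = .0167 keeps the error at about 4.2 to 4.5%. An unadjusted contrast at d = 2.8 then needs 125 per group for 90% power, and 97 per group gives 80%.

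**Not part of this fix.** Site and phase terms are a separate trade of bias against variance. With two sites crossing to the intervention and one staying control, they turn the pooled comparison into a difference in differences. Assuming equal accrual across sites, the variance of the effect rises about 4-fold with equal phases and 6-fold with 6 months of baseline and 18 of intervention. That would swamp the gain from T1 adjustment and needs its own decision.

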#### Intervention

The intervention which is administered according to clinical guidelines for conducting family meetings is comprehensively outlined in the earlier work of [name] and colleagues [32]. In summary, the guidelines incorporate: (1) principles for conducting family meetings; (2) pre-meeting procedures such as liaising with the patient/family and prioritising issues; (3) deciding who needs to attend the family meeting; (4) a procedure for conducting the meeting; and (5) strategies for follow up after the meeting, including data on whether or not the priority issues for the family carer have been addressed. The meetings are intended to take no longer than one hour.

Approximately four facilitators will be appointed at each of the participating sites to convene and conduct the family meeting/intervention. The facilitators will be nurses, doctors, social workers or psychologists with extensive clinical palliative care experience and relevant academic qualifications. Facilitators will be identified by the director of palliative care at each of the participating sites. They will receive training in administering the intervention which will incorporate conducting the family meeting according to the aforementioned guidelines; along with communications skills theory and practicum. In order to limit variation of intervention delivery at each site the training approach for all facilitators will be consistent and will be conducted face to face over the course of 1 day.

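### About eight facilitators deliver every structured family meeting, but the sample size allows for no clustering and the analysis names no facilitator level; if facilitators differ, precision and power are overstated

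*Protocol article*

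**What the plan says.** **Delivery.** The Intervention section states: "Approximately four facilitators will be appointed at each of the participating sites to convene and conduct the family meeting/intervention". They may be nurses, doctors, social workers or psychologists, and all receive the same one-day training, which is meant to limit variation in delivery. Under Research design, three sites are randomised and two of them go on to deliver SFM. About 4 x 2 = 8 facilitators therefore see all intervention carers. Under Procedure and Standard care, control carers receive usual care. Some will have a family meeting, typically not a formally structured one.

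**Analysis.** The Analyses plan uses linear mixed models for the group-by-time interaction and for the T2 and T3 contrasts, "accounting for the non-independent nature of the data in clusters". It does not say what a cluster is. The only units the article randomises are sites.

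**Sample size.** The method is "Estimated sample size for two-sample comparison of means Test Ho: m1 = m2", with "alpha = .05 (two sided"), power 0.90, means of 16.8 and 14, and SD 6 in each group. The result is 97 per group. The same paragraph says the calculation is "based on a smaller mean difference between groups of 2.4". No ICC or design effect is given at any level.

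**The concern.** This is a partially nested design. Intervention carers share a facilitator with roughly eleven others, while control carers share none. If some facilitators run better meetings than others, outcomes in the intervention group are correlated within facilitator. A site term applies equally to control and intervention carers, so it cannot absorb differences between facilitators at the same site.

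Two things are at stake. First, the standard error of the SFM effect on the GHQ may be too small, so that a few unusually good or poor facilitators are read as an effect of SFM. Aim 2 concerns routine practice, which means facilitators beyond these eight, so their variation belongs in the uncertainty. Second, the stated power is fixed in the article and assumes independent carers, although the Analyses plan itself treats the data as clustered.

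**Working it through.** **Inputs from the article:** difference 16.8 - 14 = 2.8 (2.4 in the prose); SD 6; two-sided alpha 0.05; power 0.90; 97 per group; about 8 facilitators.

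**Assumptions:** facilitator ICC 0.02, 0.05 or 0.10; one facilitator per carer; equal caseloads, m = 97/8 = 12.1; total variance 36 in both groups.

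**1. Reproduce the plan's figure.** n = 2 x 36 x (1.960 + 1.282)^2 / d^2, with (1.960 + 1.282)^2 = 10.507.
- d = 2.8: 756.5 / 7.84 = 96.5, so 97. This matches.
- d = 2.4: 756.5 / 5.76 = 131.3, so 132.

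The 97 is therefore an independent-observations figure for 2.8.

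**2. Add facilitator clustering in the SFM group only, with no site or period effects.** The design effect is DE = 1 + (m - 1) x ICC. The SE of the difference is 6 x sqrt((1 + DE)/97). Power is Phi(d/SE - 1.960). At ICC 0.05, DE = 1 + 11.1 x 0.05 = 1.56, SE = 6 x sqrt(2.56/97) = 0.974, and power = Phi(2.875 - 1.960) = 82%.

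| ICC | DE | SE | SE / naive SE | Power at 2.8 | Power at 2.4 |
|---|---|---|---|---|---|
| 0 | 1.00 | 0.862 | 1.00 | 90% | 80% |
| 0.02 | 1.22 | 0.908 | 1.05 | 87% | 75% |
| 0.05 | 1.56 | 0.974 | 1.13 | 82% | 69% |
| 0.10 | 2.11 | 1.075 | 1.25 | 74% | 61% |

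An ICC of 0.05 corresponds to a facilitator SD of 6 x sqrt(0.05) = 1.3 GHQ points.

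**3. Degrees-of-freedom penalty.** The powers in step 2 use normal critical values. A matching test compares the mean of the eight facilitator means with the control mean, using Satterthwaite degrees of freedom. In simulation it holds type I error at about 5%. Its power at 2.8 is 87.5%, 83.3%, 77.3% and 68.0% at ICC 0, 0.02, 0.05 and 0.10.

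**4. Does a site term cure it?** 4,000 trials were simulated under no effect. The assumed control split was 49 at the permanent control site and 24 at each delivering site, with four facilitators at each delivering site. The model had site fixed effects and no facilitator term. Type I error was 4.9%, 6.3%, 7.3% and 9.7% at ICC 0, 0.02, 0.05 and 0.10. An algebraic check at ICC 0.05 gives a true SE of 1.152 against 1.056 expected from the model, a ratio of 1.091. Type I error is then 2 x [1 - Phi(1.960/1.091)] = 7.2%. The same check gives 5.9% at 0.02 and 9.5% at 0.10. A site term reduces the inflation but does not remove it.

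**5. How well can the facilitator variance be estimated?** With eight facilitators, the estimate is zero when F on 7 and 89 df falls below 1/(1 + m x ICC/(1 - ICC)) times its central scale. That happens in about 41% of trials at ICC 0.02 and 25% at ICC 0.05.

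**The case against.** **The random-effects structure may be set elsewhere.** The article does not define clusters and does not exclude facilitators. A condensed article may leave this to an analysis plan that is not shown. This largely stands: a reader might infer that the plan models site only, but that is the natural reading and not a stated fact. It does not rescue the sample size, where the independence assumption is fixed in the text.

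**The ICC may be small.** Contact is a single meeting of at most an hour, run to written guidelines after common training, with fidelity checked in one meeting in six. Several disciplines may attend, so the outcome is not one person's work. This stands as a reason not to say that the intervals are too narrow as a fact. At ICC 0.02 the effect is modest. Training limits variation but does not remove it.

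**The inflation depends on the model.** A test with no site term would show about 8.3% and 11.6% type I error at ICC 0.05 and 0.10. A reader might quote those figures, but the plan does provide for clusters, so the site-adjusted figures are the fair ones.

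**The nesting is not clean.** The facilitator count is approximate, caseloads may be unequal (which would raise the design effect), and some control carers also have meetings. Control carers are un-nested only with respect to study facilitators.

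**The recruitment target is larger.** The feasibility text speaks of "providing the required sample size of 228 from the recruitment pool in 2 years". If that gave 114 per group, power at 2.8 before the degrees-of-freedom penalty would be 91%, 86% and 78% at the three ICCs. This offsets part of the loss, but the paragraph ties its 90% to 97 per group.

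**Site and period may matter more.** With three sites and one permanent control, they may dominate the uncertainty. That does not remove this level, which remains after they are adjusted for.

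**Conclusion.** The point holds in conditional form. For any positive facilitator ICC, a site-only model understates the SE of the SFM effect, and the 90% power at 97 per group is not delivered. The direction is firm. The size is not, because the article gives no facilitator ICC: over the assumed range the consequence runs from small (0.02) to material (0.05 and above). A reader might take a single figure, such as 77%, as the trial's true power. The documents do not support that. It rests on one assumed ICC, on equal caseloads, on setting site and period aside, and on a difference of 2.8 where the same paragraph names 2.4. It is worth correcting because the remedy is cheap and the stated power is unconditional.

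**What to change.** - **Data:** record the lead facilitator's ID for each SFM. Facilitators already tell the research assistant when a meeting has taken place, so this is one extra field.
- **Analyses plan:** define clusters to include facilitator. In addition to site, fit a facilitator random effect in the intervention group only, at T2 and T3, with small-sample degrees of freedom (Satterthwaite or Kenward-Roger). If the variance is estimated as zero, report that alongside the site-only result. Keep intervention carers who had no meeting in the analysis.
- **Sample size section:** say that 90% assumes no clustering and a difference of 2.8, and reconcile 2.8 with 2.4. Give power over a stated ICC range in place of one fixed value. The trial need not be enlarged.

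**Cost:** one model term, one data field and a revised paragraph. Intervals will be somewhat wider, the facilitator variance will be imprecise with about eight facilitators, and the stated power will look less favourable. The matching test gives up about 2 to 3 points of power even if facilitators do not differ (87.5% against 90%).

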##### Exclusion criteria for family carers

Under 18; incapacity to understand or speak English; unable to provide informed consent due to cognitive impairment (as assessed by the research assistant); or not agreeable to being considered the primary family carer.

For the intervention phase, patients and family carers who have already been involved in a formal family meeting as part of routine specialist palliative care will be excluded from participation. As part of routine data collection for the study we will ask each participating site to record in the medical record if a formal family meeting (ie specific meeting set up to confirm plan of care) has occurred.

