**Fig. 1 Fig1:**
[figure not shown]
Recruitment and data collection

The research assistant will then phone the family carer (or approach them in person at the hospital) to invite them to participate within 72 h of patient admission (see Fig. 1). The research assistant will give the family carer a copy of the Plain Language Statement and consent form if approaching them in person and go through it with them and obtain formal written consent. If contact has been made by phone, the research assistant will go through the content of the Plain Language Statement and consent form with them over them phone and send it to them (either by email or post) to be signed and returned by post or in person. Once the carer has consented, the research assistant will arrange a convenient time (and place) to collect time 1 data either over the phone or in person (at the hospital). Time 1 data collection will take no longer than 30 min to complete and will be conducted within 1 week from referral/admission.

The research assistant will phone the family carer when it is time to collect time 2 and 3 data and ask them if they would prefer to complete the questionnaire over the phone, in person at the hospital, or by post. Times 2 and 3 data collection will take no longer than 30 min to complete.

If the family carer is in the intervention group, the research assistant will refer them to the family meeting facilitator (who has been trained to conduct the structured family meetings) as soon as the carer has completed time1 data. Similarly, once the family meeting has been conducted (ideally within a week of time 1 data being collected) the family meeting facilitator will inform the research assistant. This study design does not allow the research assistant to be blinded to the condition to which carers are allocated.

If the family carer is in the control group, then they receive usual care for the period between time 1 and time 2 data collection.

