#### Standard care

Standard care is known to be quite heterogeneous. Family meetings are offered in all participating sites but the frequency and method of conduct varies; thus we are mindful that some control participants will receive a family meeting, although these are typically not formally structured. Our research has been designed in recognition of this and we will also collect data on the frequency of family meetings conducted in the control group.

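### Two sub-analyses run only after a null main result; the one called 'per protocol' compares carers selected on meeting receipt, so it is neither randomised nor per protocol

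*Protocol article*

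**What the plan says.** The Analyses plan makes the comparison of the intervention and control groups by linear mixed models the main analysis. It then adds a conditional step: "In the event of ‘no intervention effect’, where possible, a sub-analysis will be conducted". That step would "compare outcomes in the control group carers who did not have a meeting" "with those in the intervention group carers who had a meeting", and the plan names it a per-protocol analysis. Under the same condition, "a sub-analysis will be conducted on those that were moderately or highly distressed at time 1". The neighbouring comparison of inpatient-unit and consultancy recruits carries no such condition.

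Three other sections bear on this:

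- Standard care accepts that "some control participants will receive a family meeting, although these are typically not formally structured", and says that "we will also collect data on the frequency of family meetings conducted in the control group".
- Procedure places the intervention meeting after the T1 questionnaire: the facilitator informs the research assistant "once the family meeting has been conducted (ideally within a week of time 1 data being collected").
- Exclusion criteria for family carers removes people with an earlier meeting in one phase only: "For the intervention phase, patients and family carers who have already been involved in a formal family meeting".

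**The concern.** There are two separate faults.

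First, the meeting-based contrast keeps or drops carers according to something that happens after allocation. If having a meeting is related to how the carer would have fared anyway, the two retained sets differ even when the intervention does nothing. The label is also wrong. Usual care is the control condition and may include a meeting, so a control carer who had one has not deviated. Removing that carer changes the comparator from usual care to usual care without a meeting.

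Second, whether the intervention helps distressed carers is of interest whatever the main result. The plan asks it only after a null, and only inside the distressed subset, where nothing tests whether the effect differs from that in other carers.

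At stake is how a null trial would be read. A significant result from either sub-analysis could be taken as evidence of benefit or harm that the main comparison did not show.

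**Working it through.** **Yardstick.** The sample size section lists means 16.8 and 14 (difference 2.8), SD 6, two-sided alpha 0.05 and power 0.90. Per group, n = 2(1.960 + 1.282)² × 6² / 2.8² = 2 × 10.51 × 36 / 7.84 = 96.5, so 97, which is the stated figure. The text of the same section gives the planned difference as 2.4. A spurious difference should therefore be judged against 2.4–2.8 points.

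**Size of the selection bias.** Let p be the share of control carers who have a meeting and q the share of intervention carers who do. Let δC and δI be the differences in untreated T2 GHQ mean, meeting minus no meeting, within each group. With no treatment effect:

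- retained controls have mean = overall − p·δC
- retained intervention carers have mean = overall + (1 − q)·δI
- spurious difference (intervention − control) = p·δC + (1 − q)·δI

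A positive value means higher GHQ, so the intervention looks worse.

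The document gives none of p, q, δC or δI; all are assumed here. A link of 0.5 in log-odds of a meeting per SD of outcome corresponds to δ of roughly 0.5 × 6 = 3 points. The simulated columns use 97 per group, SD 6, T1–T2 correlation 0.5 (assumed), t-tests at T2 and 6,000 trials per row.

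| p | q | Link with prognosis | Formula | Simulated bias | False-positive rate of this contrast |
|---|---|---|---|---|---|
| 30% | 80% | none | 0 | 0.0 | about 5% |
| 10% | 95% | same direction | 0.30 + 0.15 = 0.45 | 0.5 | 8% |
| 30% | 80% | same direction | 0.90 + 0.60 = 1.50 | 1.5 | 32% |
| 50% | 80% | same direction | 1.50 + 0.60 = 2.10 | 2.0 | 46% |
| 30% | 80% | opposite directions | 0.90 − 0.60 = 0.30 | 0.3 | 5.5% |

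If the less distressed carers are the ones who meet, the sign reverses. For 30% and 80% the bias is then −1.5 points, which flatters the intervention.

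**What T1 adjustment does.** Suppose control receipt depends only on T1 GHQ (log-odds 0.7 per SD, about 30% with a meeting), attendance in the intervention group is about 82% and unrelated to GHQ, and the T1–T2 correlation is 0.6. The unadjusted contrast is then off by about 0.7 points, making the intervention look worse, and rejects in about 10% of trials. Adjusting for T1 brings this to 0.00 points and 5.0%. If receipt instead follows prognosis that T1 does not capture, 0.74 points and 15.6% remain after adjustment. Adjustment removes only the part explained by T1 GHQ.

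**Multiplicity.** Three independent tests at 0.05 would give 1 − 0.95³ = 14.3%. These tests share data. With no true effect and no selection, simulation gives 5% for the main test, about 8.5–8.7% when the distressed subset (T1 GHQ ≥15) is added, and 10.0–11.0% when the meeting-based contrast is added too (T1–T2 correlation 0.5 to 0.6).

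**What the trigger does.** At least one of the three is significant either when the main test is, or when it is not and one of the others is. That is the same event whether the others are always run or run only after a null. The trigger does not change this rate; it decides which results are ever seen.

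**The case against.** Both analyses are written down in advance, called sub-analyses and kept apart from the main analyses. The first is qualified by feasibility, and sub-analyses in general by sample size. Nothing says that they replace the main result. H1 is worded around carers who receive a meeting, so some interest in receipt is legitimate. Multiplicity rules and exploratory labels are commonly left to an analysis plan. The distressed subset is defined at baseline and so carries no post-allocation selection.

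Most of this stands, and it limits the point. The main test is sound at 5%, and the distressed analysis is faulted only for its trigger and for the missing interaction test. What remains is what the text itself fixes: the trigger, the retained sets and the label.

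A reader might infer more than the document supports:

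- **That selection would turn a failed trial positive.** The direction is unknown. In the T1-only scenario above the bias runs against the intervention, with false benefit in about 0.5% of trials.
- **That control meetings go to the more complex families.** Standard care says only that frequency and method vary.
- **That a particular bias can be quoted for this trial.** The simulations use T2 comparisons, not the planned mixed model, and ignore site clustering.
- **That deleting the trigger lowers the false-positive rate.** It does not, as shown above.
- **That a complier-average estimate is a ready replacement.** Allocation is by three sites and by phase, and the prior-meeting exclusion applies to the intervention phase only. Allocated condition is therefore a doubtful instrument.

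**Conclusion.** The point holds in this form. The meeting-based contrast selects on post-allocation events in both groups, is not a per-protocol analysis, and cannot be read as a randomised comparison. Its bias is absent if receipt is unrelated to prognosis, can nearly cancel if the links run in opposite directions, and reaches 1–2 GHQ points under moderate same-direction links. These sizes rest on assumed meeting rates and assumed links. The distressed-carer question is made to depend on a null result and lacks an interaction test. Reading all three tests at 0.05 gives about a 10–11% chance of at least one false positive before any selection. That inflation matters only if a sub-analysis is allowed to count against the main result.

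**What to change.** - Remove both conditions on a null main result, and report both analyses whatever it shows.
- State that both are exploratory and cannot overturn the main result. This sentence, not removal of the trigger, deals with multiplicity.
- Replace the distressed-only analysis with a group-by-T1-GHQ interaction in all carers, and show the estimated effect at the cut-offs given under Family carer measures (≥15 and >20).
- Drop the 'per protocol' label. Adjust the meeting-based contrast for T1 GHQ and other collected baseline predictors of meeting receipt, and report it as a non-randomised comparison.
- Add a complier-average estimate only if its assumptions are stated, given allocation by site and phase and the one-sided prior-meeting exclusion.

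The cost is wording and a little more analysis work. The interaction test will have low power, so its interval should be shown and a non-significant result should not be read as no difference.
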